#### 2.3.3. Session 3—Conception of Further Strategies Based on Personal Values

In the third and last session, the aim is to summarize the two previous sessions and record the contents discussed for later use. In this session, a concise strategy for dealing with worries will be conveyed through an exercise on the non-judgmental perception of thoughts [47]. This can be a useful skill to describe negative feelings more neutral and hence break the vicious circle of rumination. In addition, as a conclusion to the work on values, the participants should practice aligning their own action planning with a personal value. The session concludes with discussing the personal take-home messages, with participants summarizing what they have gained from the conversations.

### 2.4. Outcome Measures

This pilot study follows an explorative mixed methods approach focusing on feasibility aspects and effects of the intervention using both quantitative and qualitative data. Data will be collected from both relatives and patients to capture the factors influencing the burden of relatives in the early phase of the disease. It is known from previous studies on the late phase that, in addition to the patient’s health status and the severity and duration of the disease, other patient-related aspects influence caregiver burden [48]. For the relatives, mental health, sociodemographic factors, and personality aspects, among others, are considered predictors of burden [36]. The data collection is thus intended to provide a diverse and complete picture of the burden on relatives in the early stages of Parkinsonism.

#### 2.4.1. Effects of the Intervention

To determine whether the intervention has led to health- and stress-management-related changes in the relatives, standardized questionnaires and psychometric tests will be conducted at three time points of measurement (t0, t1, t2). The questionnaires address various parameters: personality, sense of burden, depression, cognition, quality of life, coping strategies for stress, self-management, expectation of therapy, and subjective benefit (see Table 1 for details).

Montreal Cognitive Assessment (MoCA) Blind 8.1; [38]; Parkinson’s disease caregiver burden questionnaire (PDCB) [49]; Zarit Burden Interview (ZBI) [50]; Beck’s Depression Inventory (BDI-II) [39,51]; Coping Inventory for Stressful Situations (CISS) [52]; Measurement of health-related quality of life (EQ-5D) [53]; Questionnaire for the assessment of resources and self-management skills (FERUS) [54], Therapy Expectancy and Evaluation Questionnaire (PATHEV) [55]; Credibility/Expectancy Questionnaire (CEQ) [56]; The Parkinson’s Disease Questionnaire (PDQ-39) [57]; Big-Five-Inventory 10 (BFI 10) [58].

After completion of data collection, quantitative data will be analyzed using statistical software IBM SPSS Statistics 27. Detailed descriptive analyses as well as paired-samples *t*-tests and Mann–Whitney-U-test, respectively, will be conducted, according to the distribution of the data. Subjects who drop out of the study will be included in the analysis in the sense of an intention-to-treat analysis. Table 1 provides an overview of the questionnaires and the neuropsychological test battery.

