The intervention itself is solely aimed at the non-caregiving relatives and intends to strengthen resources, thereby fostering empowerment in the course of a progressive disease. Topics of the intervention, which follows a cognitive–behavioral therapy approach, are, on the one hand, the visualization and activation of relatives’ social network of relationships, and, on the other hand, specific exercises with relatives of people with Parkinsonism to empower dealing with stressful situations possibly arising in the future. The intervention is offered online and allows participation from home to facilitate implementation into relatives’ everyday life. The key question is, therefore, a threefold feasibility analysis:Feasibility of the intervention: the feasibility will be assessed via acceptability, fit and subjective benefit.Feasibility of the manual (adherence): it is to be assessed whether all planned aspects of the intervention have been discussed or if there are other topics that will be brought up by the relatives.Feasibility of the study design: investigating the feasibility of the study design means critically reflecting on the mixed-methods approach, the process of a baseline measurement with post and follow-up assessments, as well as the validity of the questionnaire selection and the structure of the interview guide. The data from questionnaires will be used for exploratory analyses.

Against this background, the primary aim of this multicenter pilot trial following a mixed-methods approach is to develop and assess the feasibility of a preventive psychological short intervention to relatives of patients with Parkinsonism at early stages. In addition, the secondary aims are to investigate the effects and manual adherence of the intervention.

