## 2. Methods and Study Design

### 2.1. Methods

This study will be conducted at two different locations in Germany, the Department of Neurology of the University Hospital in Marburg (study number: 175/20) and the Department of Medical Psychology/Neuropsychology and Gender Studies of the Faculty of Medicine and the University Hospital Cologne of the University of Cologne (study number: 21-1061). Ten patients and ten relatives will be included as dyads per site so that a total of 20 relatives and 20 patients with Parkinsonism will be included. Recruitment will take place separately at both sites. At the Marburg site, patients and their relatives will be recruited via an internal recruitment system of the Department of Neurology at the University Hospital that lists patients with Parkinsonism who are generally interested in participating in studies. In Cologne, recruitment will be ensured via lists of study participants from previous studies. Further, e-mail distribution lists of self-help groups will be used to increase the recruitment numbers.

Inclusion criteria for patients are: (1)Patients with a clinical diagnosis of Parkinsonism according to the Movement Disorder Society (MDS) criteria [2];(2)Patients aged ≥ 18 years;(3)Hoehn and Yahr stages I–II (OFF-state).

The exclusion criteria for the patients are:(1)Hoehn and Yahr stage ≥ III (OFF-state);(2)No care requirements and/or outpatient or inpatient care;(3)Suspected dementia according to physicians’ reports and (third-party) anamnesis.

Inclusion criteria for non-caregiving relatives are:(1)Partners of people diagnosed with Parkinsonism, living together in the same household;(2)Age ≥ 18 years;(3)Not involved in informal caregiving of the subject with Parkinsonism;(4)Willingness to use telemedicine, availability of a PC or tablet with stable internet connection;(5)No cognitive impairment (operationalized by the Montreal Cognitive Assessment [MoCA] [38], Blind Version ≥ 19; the MoCA Blind, which is suitable for online administration and therefore used here, is reduced to 22 items and converted back to 30 points maximum. A total of 19 points in the MoCA Blind version correspond to 26 points in the original MoCA “Full”);

Exclusion criteria for the relatives are: (1)Own caregiving requirement;(2)Severe depression (operationalized by the Beck’s Depression Inventory-II [BDI-II] ≥ 29 points) [39].

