### 2.2. Study Design

The patients and their relatives will be informed verbally and in writing about their participation in the study. By signing the consent form, they are included in the study. Figure 1 depicts the three time points of measurement: baseline (t0), post-testing immediately after the end of the intervention (t1), and follow-up (FU) at 6 weeks post-intervention (t2). The intervention is to be understood as a preventive psychological short intervention for relatives. Patients will not participate in the intervention. No remuneration will be paid to the participants.

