## 4. Conclusions

This study aims to test a preventive e-mental health offer for relatives of people with Parkinsonism. It will be apparent whether the target group accepts this offer and what suggestions and feedback are revealed in the evaluation. With the help of feedback, especially from the interviews, the psychosocial intervention will be further developed to ensure that the offer is oriented according to the needs of the relatives. After evaluating the pilot study, a modification of the intervention and the study design is planned, relying on the findings. Based on this, a multicenter randomized, controlled trial will be implemented.

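### The rank test named as the alternative to the paired t-test is for independent samples, but the effect comparisons described are within the same relatives

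*Protocol article*

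**What the plan says.** Section 2.4.1 states the purpose of the quantitative effect analysis: "To determine whether the intervention has led to health- and stress-management-related changes in the relatives". It plans descriptive analyses and paired-samples t-tests, and continues "Mann–Whitney-U-test, respectively, will be conducted, according to the distribution of the data". No other inferential test is named for the effects.

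The design around that sentence is as follows.

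- **Sample.** Section 2.1 recruits ten dyads at each of two sites, so that "a total of 20 relatives and 20 patients with Parkinsonism will be included".
- **Time points.** Section 2.2 sets baseline (t0), the end of the intervention (t1) and six weeks after it (t2).
- **Patients.** Section 2.2 says "Patients will not participate in the intervention". Table 1 measures them at baseline only.
- **Control group.** There is none. The Conclusions place the controlled comparison later: "Based on this, a multicenter randomized, controlled trial will be implemented".
- **Repeated outcomes in relatives (Table 1).** PDCB, BDI-II, EQ-5D, CISS and FERUS at all three times; PATHEV at t0 and t1.
- **Status.** The Introduction makes effects a secondary aim and says "The data from questionnaires will be used for exploratory analyses".

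**The concern.** The Mann–Whitney test ranks two sets of scores as if they came from different people. Here the two sets are the same relatives at two times. When a person's scores are positively correlated, as is expected of repeated questionnaires, the test overstates the variability of the difference under no change, and its p-values no longer mean what they claim.

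The branch could well be used. The study targets relatives without distress symptoms and excludes severe depression, so scores on burden and depression scales may bunch near the floor and be skewed. The p-values from this branch would then come from a test that does not match the design, in a pilot meant to inform a later randomized trial.

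**Working it through.** **Step 1. What is the test standing in for?** The word respectively, and the choice by distribution, set Mann–Whitney against the paired-samples t-test as its non-normal alternative. The t-test in that sentence is paired, so the comparison it serves is paired.

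**Step 2. Is there an independent-groups comparison it could serve?** There is no control arm. Patients are untreated and have no t1 or t2 data. A patient–relative comparison at baseline would also be paired, since they enrol as dyads. Two sites (section 2.1) and a dropout analysis (section 2.4.4) could supply independent groups, but the article attaches this test to neither. The Wilcoxon signed-rank test appears nowhere.

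**Step 3. Inputs for the size of the error.** From the article: n = 20 relatives. Assumed, because the article gives none: two-sided alpha 0.05, within-person correlation rho, and the shape of the scores. There is no stated figure to reproduce.

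**Step 4. Why the level is wrong.** To leading order, the Mann–Whitney statistic is proportional to the sum over relatives of F(t1 score) − F(t0 score), where F is the score distribution. Its variance under pairing is (1 − rho_S) times the variance the test assumes, where rho_S is the Spearman correlation. For an underlying bivariate normal, rho_S = (6/π)·arcsin(rho/2).

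- rho = 0.3: rho_S = 0.288; √(1 − 0.288) = 0.844; effective critical value 1.96/0.844 = 2.32; two-sided error about 2.0%.
- rho = 0.5: rho_S = 0.483; √(1 − 0.483) = 0.719; 1.96/0.719 = 2.73; error about 0.6%.

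This is a large-sample approximation. Simulation gives the values at n = 20.

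**Step 5. Type I error by simulation** (20 pairs, 10,000 replicates, normal scores):

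| rho | Mann–Whitney | Signed-rank |
|---|---|---|
| −0.3 | 8.3% | 5.0% |
| 0 | 4.7% | 5.0% |
| 0.3 | 2.1% | 5.2% |
| 0.5 | 1.0% | 4.6% |
| 0.7 | 0.14% | 5.1% |
| 0.8 | 0.04% | 4.8% |

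Skewed (lognormal) scores give nearly the same Mann–Whitney values. They should, because a common monotone transformation of both time points leaves the ranks unchanged.

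**Step 6. Power for a 0.5 SD shift.** The branch applies when scores are not normal, so the skewed cases are the relevant ones. Scores are lognormal with a Gaussian copula and a pure shift, 4,000 replicates. Each cell gives Mann–Whitney vs signed-rank.

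| rho | Moderate skew (sigma 0.5) | Strong skew (sigma 1) |
|---|---|---|
| 0.3 | 47% vs 52% | 89% vs 77% |
| 0.5 | 47% vs 64% | 92% vs 85% |
| 0.7 | 47% vs 82% | 94% vs 93% |
| 0.8 | 47% vs 93% | 95% vs 96% |

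A repeat of steps 5 and 6 with a different random seed gave the same picture.

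The shift size matters too. For a 0.3 SD shift under strong skew (10,000 replicates), the figures are 60% vs 57% at rho 0.5, 62% vs 72% at rho 0.7 and 63% vs 82% at rho 0.8.

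**The case against.** The strongest reply is about weight. Feasibility is the primary aim, effects are secondary, and the questionnaire analyses are declared exploratory. The Discussion says that 20 participants cannot support reliable statements about impact. No decision rule rests on these p-values, and the Conclusions look to feedback, mainly from the interviews, to shape the next version. With positive correlation the error is in the cautious direction: too few claims of an effect, not too many. All of this stands and limits the severity. It does not make the test right, since the disclaimer concerns sample size and not whether the test fits the design.

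It can also be said that section 2.4.1 does not list its comparisons, so an independent-groups use is possible. That is fair, but the article describes none for this test, and such a use could not replace a paired t-test according to the distribution of the data.

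A reader might go further and infer that this branch loses most of the sensitivity to within-person change. The documents do not support that. They give no correlation, distribution or effect size, and the assumed cases in step 6 run from a large loss to a reversal. Nor is strong conservatism certain: it needs clearly positive correlation, and at rho 0.3 the error is about 2%.

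Choosing a test by distribution is common in declared exploratory work. Fixing a test for each scale, or adding particular interval estimates, is detail for an analysis plan. Neither is part of this point.

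**Conclusion.** The sentence is wrong as written. It gives an independent-samples test as the counterpart of a paired t-test, in a single-group study whose described effect comparisons are all within the same 20 relatives. This is a stated choice, not something left to a fuller document, and nothing else in the article corrects it.

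The firm consequences are a wrong null distribution and discarded pairing: a type I error of about 1% down to under 0.1% at a nominal 5%, given 20 pairs, two-sided alpha 0.05 and assumed correlations of 0.5 to 0.8. Loss of power is possible and can be large under moderate skew, but it is not general. The severity is moderate. The feasibility objective is untouched, and the p-values affected belong to a secondary, exploratory analysis.

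**What to change.** In section 2.4.1, replace the Mann–Whitney U test with the Wilcoxon signed-rank test for all within-relative comparisons between t0, t1 and t2. Keep Mann–Whitney only if a comparison of independent groups is intended, such as between sites, and in that case name the comparison.

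The cost is one phrase. Sample size, questionnaires, visits and burden on participants do not change, and the correction can be made at any time before the data are analysed.

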#### 2.4.4. Feasibility of the Study Design

To examine the feasibility of the study, the test battery will also be critically examined regarding length and expected benefit. The feasibility of the study design will be discussed in an expert panel, considering the results of the interviews and the completed questionnaires. In addition, a dropout analysis will be conducted to evaluate the reasons for participants dropping out of the study.

An overview of the feasibility analysis is summarized in Table 2.

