**Relatives**				
Sociodemografic data	Personal data	x		
Montreal Assessment (Moca) Blind 8.1	Cognition	x		
Parkinson’s disease caregiver burden questionnaire (PDCB)	Burden on family carergiver	x	x	x
Zarit Burden Interview (ZBI)	Burden on family carergiver	x		
Beck Depression inventory (BDI-II)	Depression	x	x	x
Health-related quality of life (EQ-5D)	Health-related quality of life	x	x	x
Coping Inventory for Dealing with Stressful Situations (CISS)	Coping strategies for stressful situations	x	x	x
Questionnaire on Health-Related Resources and Self-Management Skills (FERUS)	Health-related self-management strategies	x	x	x
Therapy Expectancy and Evaluation Questionnaire (PATHEV)	Therapy Expectancy	x	x	
Big-Five-Inventory 10 (BFI)	Personality	x		
Subjective Benefit (Credibility/Expectancy Questionnaire (CEQ))	Subjective Benefit		x	
Semi-structured Interview	Feasibility of the intervention		x	x

**Table 2 brainsci-12-00442-t002:** Feasibility analysis.

Outcome	Measurement Instruments	Operationalisation
Feasibility of the Intervention		
Acceptance	Interview	Willingness of the target group to participate
		Reasons for participation
		Evaluation of the digital intervention
Fit	Interview	Scope of the intervention
		Effort for the relatives
		Choice of timing
		Suggestions for optimization
		Overall assessment
Subjective Benefit	Interview	Particularly helpful aspects
		Psychosocial changes that the relatives notice about themselves
Evaluation of the intervention	Questionnaire (Filled in by the relative)	Questionnaires for the evaluation of each session
Feasibility of the intervention manual		
Adherence	Questionnaire (Filled in by Advisor)	Assess whether all intended aspects of the intervention have been discussed. A maximum of 14 points can be achieved
Feasibility of the study design		
Quality criteria	Expert panel	Quantiative: Validity, reliability, objectivity Qualitative: Transparency, intersubjectivity, range Drop-Out-Analysis

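### Dropouts are promised a place in the effect analysis, but the paired t-test named omits anyone without a later value and no imputation is stated

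*Protocol article*

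**What the plan says.** Section 2.1 describes one group and no comparator: "a total of 20 relatives and 20 patients with Parkinsonism will be included". Section 2.2 sets three measurement times for the relatives: baseline (t0), the end of the intervention (t1) and six weeks later (t2). Table 1 lists five relative scales at all three times: PDCB, BDI-II, EQ-5D, CISS and FERUS.

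Section 2.4.1 names descriptive analyses, then paired-samples t-tests and "Mann–Whitney-U-test, respectively", which "will be conducted, according to the distribution of the data". The next sentence fixes the analysis population: "Subjects who drop out of the study will be included in the analysis in the sense of an intention-to-treat analysis".

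The only other provision on dropout is in Section 2.4.4: "a dropout analysis will be conducted to evaluate the reasons for participants dropping out of the study". On the standing of these data, the Introduction says: "The data from questionnaires will be used for exploratory analyses". The Discussion adds that 20 participants are too few for dependable conclusions about effect.

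**The concern.** Two adjacent sentences in Section 2.4.1 do not fit together. With a single group, intention-to-treat cannot mean analysis by allocated arm. It can only mean that enrolled relatives stay in the analysis after dropping out. A paired t-test needs both values from the same person, so it does not deliver that population by itself. Mann–Whitney U does not close the gap, because it ignores the pairing that a before–after comparison depends on.

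The main risk is one of labelling. A reader told that the result is intention-to-treat would take it to describe all 20 enrolled relatives, when it describes those who supplied the later questionnaire. If the gap were instead filled at analysis time by an unstated imputation rule, that rule would itself move the estimate.

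**Working it through.** **Inputs.** From the article: 20 relatives (Section 2.1), times t0, t1 and t2 (Section 2.2), and the two tests and the population rule (Section 2.4.1). The article gives no alpha, power, effect size, SD or dropout rate and no derivation of the sample size, so there is no figure to reproduce. Everything below on dropout, correlation, effect size, alpha and power is an assumption for illustration.

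**Step 1: who enters the paired t-test.** The test uses d = y(later) − y(t0). If the later value is missing, d does not exist. The usable number is 20 × (1 − dropout). Power comes from the noncentral t distribution with n − 1 degrees of freedom and noncentrality (standardised change) × √n, two-sided 5%.

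| Assumed dropout | Pairs used | Power at standardised change 0.5 | Change detectable with 80% power (SD of change) |
|---|---|---|---|
| 0% | 20 | 0.57 | 0.66 |
| 10% | 18 | 0.52 | 0.70 |
| 20% | 16 | 0.47 | 0.75 |
| 30% | 14 | 0.41 | 0.81 |

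**Step 2: the same data under three treatments.** One simulated data set of 20 relatives with 4 follow-up values missing gave:

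- Paired t-test as named: 16 pairs, 15 degrees of freedom, mean reduction 2.50.
- Paired t-test with t0 substituted for the missing values: 20 pairs, 19 degrees of freedom, mean reduction 2.00, which is 2.50 × 16/20.
- Mann–Whitney U: 20 baseline against 16 follow-up values. The four dropouts' baselines are kept, but those relatives contribute no change.

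A paired test can therefore include dropouts only after an imputation rule, and the choice of rule changes the answer. Substituting t0 is used here only to show this.

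**Step 3: Mann–Whitney U on paired data.** With complete data on 20 people, no true change and 5,000 simulated data sets per setting, its rejection rate against a nominal 0.05 was about 0.009, 0.001 and 0.000 for assumed within-person correlations of 0.5, 0.7 and 0.8. Treating the two time points as independent overstates the variance of the difference, so the test is far too conservative for this comparison.

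**Step 4: what a mixed model would gain.** The simulations used n = 20 and dropout that depended on earlier scores, about 10% by t1 and 18% by t2 (about 11% and 20% in one run). In two runs with a true change of −0.40 SD, complete pairs gave −0.37 both times and the mixed model gave −0.39 and −0.41. In a third run the two methods differed by about 0.03 SD, with a trial-to-trial SD of 0.224 for complete pairs and 0.226 for the mixed model. The difference is about 0.03/0.22 ≈ 0.14, or one-seventh of one trial's sampling error. The gain in accuracy is small and there was no gain in precision for this contrast.

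**The case against.** The strongest reply is that an article may fix the analysis population and leave the handling of missing values to a fuller document. A paired t-test after imputation would use all 20 relatives. This stands as far as it goes: the absence of an imputation rule would be no finding by itself. What remains is that the article states both the population and the tests, and the paired test as stated does not give that population.

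Other points also stand. A relative who stops the sessions but completes the questionnaires is still analysed. One who misses only t2 still enters the t0–t1 comparison, and the descriptive analyses can include dropouts. The primary aim is feasibility, and by the simulations above a mixed model would move the estimate only slightly.

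A reader might infer more than the article supports:

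- *That every named test is paired, so dropouts can never be included.* Mann–Whitney U is an independent-samples test, and imputation would allow a paired test to use everyone.
- *That baseline values will be carried forward, pulling change towards zero.* The article never mentions this.
- *That the SDs of change will be distorted as inputs to the size of the next trial.* The Discussion and Conclusions say the pilot prepares a randomised trial, but they describe refining the intervention and the design. They do not say that these SDs will be used for sample size.

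**Conclusion.** The point holds in a limited form. The stated population and the stated paired test do not match, and Mann–Whitney U does not address within-person change. Without further provision, the effect result would be a completer analysis labelled intention-to-treat.

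The size depends on a dropout rate the article does not give. With no dropout the paired t-test already covers all 20 relatives and only the problem with Mann–Whitney U remains. At an assumed 20%, the test uses 16, and the change detectable with 80% power rises from 0.66 to 0.75 SD of change. The consequence is modest because the analysis is secondary and exploratory and the authors already disclaim reliable effect statements. The reason to change the text is to deliver the population it promises, not to gain precision.

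**What to change.** For PDCB, BDI-II, EQ-5D, CISS and FERUS, state one linear mixed model per scale, with time as a three-level factor and a random intercept per relative, fitted to all available observations from all enrolled relatives. Report t1–t0 and t2–t0 change with 95% confidence intervals. Keep the paired t-test as a sensitivity analysis labelled as completers only, and replace Mann–Whitney U with the Wilcoxon signed-rank test for skewed scales.

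The cost is a few sentences. The model can be fitted in the SPSS version already named, and no data collection changes. The model assumes that values are missing at random, that residuals are approximately normal and, with a random intercept only, that the three time points are equally correlated. These are hard to check at n = 20. Normality may be doubtful for depression and burden scores in relatives chosen for not yet having distress, so the signed-rank result should be shown beside the model for those scales. A relative with only a baseline value enters the model but carries little information about change.
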